## Abstract

Between 2018 and 2022 the Liberian Government implemented the National Community Health Assistant (NCHA) program to improve provision of maternal and child health care to underserved rural areas of the country. Whereas the contributions of this and similar community health worker (CHW) based healthcare programs have been associated with improved process measures, the impact of a governmental CHW program at scale on child mortality has not been fully established. We will conduct a cluster sampled, community-based survey with landmark event calendars to retrospectively assess child births and deaths among all children born to women in the Grand Bassa District of Liberia. We will use a mixed effects Cox proportional hazards model, taking advantage of the staggered program implementation in Grand Bassa districts over a period of 4 years to compare rates of under-5 child mortality between the pre- and post-NCHA program implementation periods. This study will be the first to estimate the impact of the Liberian NCHA program on under-5 mortality.

## Introduction

Under-5 mortality (U5M) has been reduced globally from 93 deaths per 1,000 live births in 1990 to 38 per 1,000 live births in 2019. Nevertheless, 1 in 13 children continue to die before their fifth birthday in sub-Saharan Africa. According to the World Health Organization, most of the deaths are due to preventable and treatable diseases [1].

Liberia ranks among the worst nations globally in child health outcomes, with U5M rate estimated at 93 per 1000 live births [2]. Remote areas are facing the greatest burden of mortality because of poor access and utilization of health care services [3]. The primary causes of U5M in the region are malaria, diarrhea and acute respiratory infections (ARI) [4, 5], which are all preventable and treatable with health interventions that are feasible for implementation in low-income countries [6].

Many countries have adopted integrated Community Case Management (iCCM) strategies to address the causes and reduce U5M. Community health workers (CHWs) are at the core of many iCCM strategies. They act within their local community and provide services such as treatment of uncomplicated childhood diseases and referring complicated cases to health facilities [7]. iCCM interventions have been shown to reduce U5M due to an increased treatment of malaria, ARI and diarrhea [8–14].

In June, 2016, the Liberian Ministry of Health (MOH) initiated a national professionalized, incentivized, and clinically supervised community health worker cadre known as Community Health Assistants (CHA). These CHAs are embedded within the public-sector health workforce, with the goal of extending the reach of the country’s primary health care system to an estimated 1.2 million people through a standardized national community health model. The CHAs provide a package of health care services and epidemic surveillance within communities and households on an equitable basis.

Although numerous studies have demonstrated improvements in child outcomes with iCCM interventions, evidence around the effects of government-run, CHW-delivered healthcare on child mortality in rural areas of sub-Saharan Africa is limited. Our central hypothesis is that the National Community Health Assistant (NCHA) program in Liberia reduced U5M in rural Liberia. To test this hypothesis, we will conduct a large, population-representative survey across a major county in Liberia, and use a mixed effects Cox proportional hazards model to retrospectively compare mortality in the pre- and post-implementation periods in order to estimate the effect of the CHA program on U5M.

## Method

### Study setting and population

Data collection did start in Grand Bassa county in January 2022. The county encompasses an area of 7,936 square kilometers and had an estimated total population of 224,839 in 2008 [15]. The target population of the NCHA are households in remote communities. Remote communities are defined as having a distance of at least 5 km to the nearest health facility. Based on a county-wide community GIS mapping exercise conducted by LMH immediately before program implementation, 1,733 communities were identified as remote, totaling 23,702 households and approximately 13,400 people and 20,900 children under the age of five years. The remote population is predominantly poor and levels of education are low. In S1 Table we show descriptive statistics for the study population. The study has been registered at clinicaltrials.gov [NCT: NCT05123378]. Approval for the study was obtained from the University of Liberia-Pacific Institute for Research and Evaluation Institutional Review Board (18^th^ of November 2021, 18-11-140) and Advarra Institutional Review Board (25^th^ of January 2021, Pro00048901), United States.

### Community health worker intervention

#### The program

As part of the post-Ebola investment plan for building a resilient health system in Liberia 2015–2021, the MOH prioritized the establishment of a robust cadre of community health workers in remote communities that were situated more than 5 km from the nearest health facility. Through the NCHA program, members of remote communities select their CHA. Those selected by their communities have to fulfil eligibility requirements, including being permanent residents in the community, aged 18 to 50 years, possess basic writing and math skills, be physically and mentally fit and must be fluent in the dialect spoken in their community. Once selected, CHAs complete a standardized training curriculum in community health and surveillance, child health and maternal and neonatal health. Services are covering treatment of diarrhea, ARI, and malaria following iCCM protocols, as well as family planning and birth preparedness. Since 2020 COVID-education and -referral has also been included in the CHAs work. Everyone in the communities more than 5 km from the nearest health facility is eligible to use the program directly or indirectly. CHAs are compensated with a monthly cash incentive of US $70 for about 20 hours of work per week. Program implementation is preceded by community engagement activities, which involves obtaining the support and advice of community leaders.

#### Implementation

The Liberian NCHA program was initiated in a stepwise manner across the eight districts of Grand Bassa County by the government of Liberia beginning in September 2018. It is planned to conclude in June 2022 (Fig 1). We will take advantage of this staggered implementation to form a study design similar in structure to a stepped wedge cluster randomized trial. However, the order of implementation was not randomized; judged by the Liberian MOH districts with more need for health interventions were prioritized in the intervention roll out. The staggering of implementation was conducted for operational and logistical reasons, rather than to facilitate an evaluation.

**Fig 1 pone.0272172.g001:**
[figure not shown]
National Community Health Assistant (NCHA) program implementation schedule in Grand Bassa, Liberia. Source: [name] based on data from Humanitarian Data Exchange [16] under a CC BY license.

### Study design

Starting in January 2022, we will conduct a census to assess U5M among the children of all women who complete the survey. The study is registered at clinicaltrials.gov (NCT05123378).

### Data collection

#### Impact assessment survey

In the 2022 impact assessment survey, we will collect data on births and child deaths from mothers aged 15 to 49 in all eight health districts of Grand Bassa (see S2 Table). We will use a survey tool based on the validated Demographic and Health Survey (DHS) that includes a full birth history, as well as questions on socioeconomic status, education, and covariates that we expect to be associated with our endpoints. We will supplement this dataset with geographic and community-level covariates obtained through a separate district mapping process. Whenever possible, the survey will be conducted in Liberian English. If a respondent speaks only Bassa, a local dialect without a commonly used written form, the enumerator will do on-the-spot translation, which they will be trained to do. We will obtain death dates using the standard Demographic and Health Survey approach, augmented with recall-enhanced elicitation. For the recall-enhanced elicitation, mothers are asked to recall all their children death dates if occurred within the last four years. The same method has been applied in similar settings by Nyqvist, Guariso [11]. Anchoring methods with landmark events will be used in the questionnaire to foster the outcome documentation [17]. We will use a calendar developed specific to Grand Bassa County, providing landmark events helping to clearly mark the reference period. Reluctance to report U5M is not expected to vary systematically by program implementation date. All participants gave (verbal/written) informed consent to participate. Written informed consent was obtained from a parent or guardian for participants under 16 years old.

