### Statistical analysis

The Liberian NCHA intervention and data collection will provide a survival data set for U5M at the community level, covering a time period from January 2018 till August 2022. To estimate program effects on U5M we will use a mixed effects Cox proportional hazards model.

Our primary outcome of interest will be U5M at the community level. Our primary exposure of interest will presence of the NCHA program. Sensitivity analyses will allow for the possibility of a time-varying treatment effect. Children will be included in the risk set from their date of birth or January 2018 (starting date of the panel), whichever is later, until their death, fifth birthday or date of the survey in 2022. Children born before implementation who remain under observation at the implementation date in their community will provide observation time to both the pre- and post-observation time periods. We will fit a mixed effects Cox proportional hazards model with a random effect at the community level to estimate effect of the NCHA program on mortality. To mitigate bias due to unobserved time-invariant confounders that were caused by the non-randomized implementation schedule of the program, we will include a fixed effect at the district level. We will also control for baseline demographic and geographic covariates.

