There are limitations to the design of this study. First, the order of implementation by district was non-randomized. Because the districts with the worst health outcomes were targeted by the intervention first, our estimate of the intervention effect estimate may be biased. Nonetheless, the stepped approach to implementation, availability of pre- and post-implementation data in the districts, and our use of district fixed effects and community covariates all enhance the causal inference of this study design. Second, the random effects at the community level rely on an assumption of minimal correlation of unobserved confounders with NCHA program exposure. Third, the data for our outcome relies on endline survey data, thus selective migration by intervention implementation date potentially causes bias in the main estimates. To address this, we will include a sensitivity analysis that limits the analysis only to those mothers who report living in the implementation area for the full study period. Third, U5M is assessed in the survey design by recall of such events in the last four years. There may be bias associated with mothers not remembering the correct birth/death dates of children. We will assume that this recall bias (and related biases, e.g. mothers’ reluctance to discuss child deaths) is minimal and does not differ significantly by geography or intervention status date. To mitigate to this source of bias and increase the validity of death reporting, we will employ a landmark event calendar, which has been previously shown to improve precision of event reporting [17]. Finally, the fidelity of implementation is not a component of this impact study, but is the focus of ongoing program evaluation to measure dose, coverage and effect of contextual factors including health facility readiness and the COVID-19 pandemic.

Prior studies have demonstrated improvement in process measures from implementation of small scale governmental CHW programs in similar settings including Liberia [18, 19]. Whereas Nyqvist, Guariso [11] were able to randomize program exposure across communities, the program was different from our evaluation in that it is was operated by a non-governmental organization. Our study will add to the literature by providing evidence from a large scale, governmental-led CHW program.

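### Enhanced death recall reaches back four years from interview but risk time starts in January 2018, so up to eight months of counted time, all pre-program, get weaker ascertainment

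*Protocol article*

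**What the plan says.** The protocol article gives two time frames for the outcome.

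- **Recall.** Under Impact assessment survey, the tool is one "that includes a full birth history, as well as questions on socioeconomic status". On dates of death: "We will obtain death dates using the standard Demographic and Health Survey approach, augmented with recall-enhanced elicitation". In the enhanced part, "mothers are asked to recall all their children death dates if occurred within the last four years". The Discussion, under limitations, gives only the shorter frame: "U5M is assessed in the survey design by recall of such events in the last four years". It then assumes that recall error is small and similar across areas and program timing.
- **Risk time.** Under Statistical analysis: "Children will be included in the risk set from their date of birth or January 2018 (starting date of the panel), whichever is later", followed up "until their death, fifth birthday or date of the survey in 2022". The data set is described as "covering a time period from January 2018 till August 2022".

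Roll-out is described under Implementation as "beginning in September 2018" and as planned to finish in June 2022. Study setting and population dates the start of data collection to January 2022. The stated model has a community random effect, district fixed effects and baseline covariates. No calendar-time term is stated.

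**The concern.** The panel start is a fixed date, whereas the recall window is worded relative to the interview. The two coincide only for an interview at the very start of January 2022. Each later interview leaves some early 2018 risk time that counts in the denominator but whose deaths are not covered by the enhanced prompt. Because roll-out began in September 2018, that time lies wholly on the pre-program side of the comparison.

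The investigators added the prompt and the landmark calendar to improve death reporting, so they evidently expect plain recall to be less good. If it is, pre-program deaths are under-recorded relative to post-program deaths and the program effect is biased. The relative loss is greatest in the first-phase districts, which have the shortest pre-program period and which the Discussion describes as having the worst health outcomes. The mismatch also works against the article's own assumption that recall error is unrelated to program timing.

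**Working it through.** No figure in the plan addresses this point. The stated 82% power comes from a simulation whose variance components are not given, and it is not at issue here.

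**Step 1: the gap.** Count months from 1 January 2018. An interview at month T has a window opening at T − 48, so the uncovered risk time is g = T − 48.

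| Interview date | T | g (months) |
|---|---|---|
| 1 January 2022 | 48 | 0 |
| End of April 2022 | 52 | 4 |
| End of June 2022 | 54 | 6 |
| End of August 2022 | 56 | 8 |

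The maximum is 8 of 56 months (14%). With interviews spread evenly over T = 48 to 56 (assumption), the mean gap is 4 months and mean follow-up is 52 months, so 4/52 = 7.7% of the panel is uncovered.

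**Step 2: where it falls.** The program starts no earlier than September 2018, month 8. Since g ≤ 8, all uncovered time is pre-program in every district. In a first-phase district the pre-program period is about 8 months, so the mean uncovered share is 4/8 = 50%.

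**Step 3: possible bias.** Let f be the share of deaths in the gap that go unrecorded. The article gives no value for it. Assume a constant hazard, stable numbers of children and four phases of equal size starting at months 8, 23, 38 and 53. The first and last starts follow the stated dates; the middle two are illustrative.

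With no true effect, the observed pre-program rate in a phase is c = 1 − f × 4/pre times the true rate. Mantel-Haenszel weights are w = pre × post/52, and the stratified rate ratio is Σw / Σ(w × c).

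| Phase start (month) | Mean pre | Mean post | w | c, f = 25% | c, f = 50% |
|---|---|---|---|---|---|
| 8 | 8.00 | 44.00 | 6.769 | 0.875 | 0.750 |
| 23 | 23.00 | 29.00 | 12.827 | 0.957 | 0.913 |
| 38 | 38.00 | 14.00 | 10.231 | 0.974 | 0.947 |
| 53 | 51.44 | 0.56 | 0.556 | 0.981 | 0.961 |

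- f = 0: 30.383/30.383 = 1.00.
- f = 25%: 30.383/28.699 = 1.06.
- f = 50%: 30.383/27.016 = 1.12.

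A Poisson fit in monthly bins, in which the mean gap rounds down to 3.5 months, gives 1.05 and 1.10.

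**Step 4: sensitivity to phase dates.** The same formula gives, at f = 25% and 50%:

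- middle phases early (months 14 and 20): 1.08 and 1.17;
- middle phases late (months 35 and 45): 1.06 and 1.12.

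Under the planning effect, a hazard ratio of 0.75, evenly spaced phases give 0.75 × 1.059 = 0.79 and 0.75 × 1.125 = 0.84. Across the three sets of dates the ranges are 0.79-0.81 and 0.84-0.88.

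**The case against.** The strongest reply is that no deaths need be missing. The enhanced prompt is added to a full birth history that has no four-year limit, so a death in March 2018 is asked about whenever the mother is interviewed. This stands. A reader might infer from the four-year wording, especially in the Discussion, that early 2018 deaths are uncounted while their person-time is counted. The documents do not support that: the survey section says otherwise, and the Discussion sentence is better treated as a description to be reconciled with it. What remains is weaker ascertainment of unknown size.

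Second, the four-year wording may be shorthand for the panel, since January 2018 to January 2022 is exactly four years, and no start date is given for the landmark calendar. That is possible, but the prompt as written moves with the interview date.

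Third, no last interview date is stated. August 2022 is inferred from the data span together with the rule that follow-up ends at the survey. The inference is reasonable, and an end-of-April interview already leaves 4 months uncovered. The loss of the whole first-phase pre-program period, however, applies only to interviews at the very end of August.

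Fourth, a reader might infer that the mismatch could create a false benefit. That would need calendar-time adjustment together with interviews that proceed district by district. Under those two additions the null hazard ratio at 50% missed could fall anywhere from 0.91 to 1.10, depending on district order. The article states neither, so this is not a finding about the plan as written.

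**Conclusion.** The recall window and the risk window do not match, and the uncovered time lies entirely on the pre-program side: 0 to 8 months per interview, about 4 on average under evenly spread interviews, and about half of the first-phase pre-program time. Ascertainment may therefore differ by program status, so the assumption that recall bias is unrelated to program timing needs qualifying.

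The effect on the estimate cannot be fixed from the article. It is zero if the birth history captures these deaths in full. If some are missed, the model as described is biased towards no benefit: a null hazard ratio of about 1.05-1.06 at 25% missed and 1.10-1.12 at 50%, somewhat more if the middle phases started early. These figures rest on assumed loss shares, interview spread, phase sizes and intermediate phase dates. The flaw is thus conservative as the analysis stands, but it could mask part of a real effect, and it is cheap to correct.

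**What to change.** 1. For remaining interviews, word the enhanced prompt as all child deaths since January 2018, and make sure the landmark calendar reaches back to that date. Record the change of prompt by interview date so that it can be examined in the analysis.
2. Pre-specify a sensitivity analysis in which each child's risk time starts at the latest of birth, January 2018 and 48 months before the mother's interview.
3. Reconcile the survey section with the Discussion by stating whether deaths more than four years before interview enter the outcome through the full birth history.
4. Qualify the non-differential recall assumption: coverage by the enhanced recall differs between early pre-program time and all later time.

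The cost is one reworded question, up to eight more months on the calendar if it does not already cover them, one extra analysis and a text correction. There are three downsides: slightly longer recall in late interviews, a prompt that changes part-way through the survey, and a sensitivity analysis that discards about half of the first-phase pre-program time. Because of the last, it should support the primary analysis, not replace it.

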#### Survey sample selection

The impact assessment survey will be a full census; all 1,733 remote target communities in Grand Bassa will be selected and all households within selected communities will be surveyed. Following the NCHA program definition, remote communities are defined as having a distance of at least 5 km to the nearest health facility. Within each household the survey population will consist of all women of reproductive age who are at least 15 years old (15–49). We selected the sample size to power our analysis using a mixed effects Cox proportional hazards model based on the assumption of a 25% decrease in the hazard of U5M following program implementation (see power calculation below).

### Statistical analysis

The Liberian NCHA intervention and data collection will provide a survival data set for U5M at the community level, covering a time period from January 2018 till August 2022. To estimate program effects on U5M we will use a mixed effects Cox proportional hazards model.

Our primary outcome of interest will be U5M at the community level. Our primary exposure of interest will presence of the NCHA program. Sensitivity analyses will allow for the possibility of a time-varying treatment effect. Children will be included in the risk set from their date of birth or January 2018 (starting date of the panel), whichever is later, until their death, fifth birthday or date of the survey in 2022. Children born before implementation who remain under observation at the implementation date in their community will provide observation time to both the pre- and post-observation time periods. We will fit a mixed effects Cox proportional hazards model with a random effect at the community level to estimate effect of the NCHA program on mortality. To mitigate bias due to unobserved time-invariant confounders that were caused by the non-randomized implementation schedule of the program, we will include a fixed effect at the district level. We will also control for baseline demographic and geographic covariates.

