## Discussion

This study will estimate the impact of Liberian NCHA program including iCCM and perinatal care support in remote Liberia on U5M. The staggered implementation of scale up within Grand Bassa offers a unique opportunity to evaluate the effectiveness of this program on a population scale. The analysis will allow us to evaluate the implementation of a critical healthcare delivery program by the Liberian Ministry of Health on U5M within the target communities.

There are multiple unique aspects of this study which will enhance both its scope and generalizability. The total population census with a program coverage of 1,753 communities and 23,702 households in the Grand Bassa county of Liberia, we will take advantage of a notably large sample size. The fact that the NCHA program is being implemented staggered across eight study health districts in four phases also gives us the opportunity to use a mixed effects Cox proportional hazards model with a random effect by community and district fixed effects to compare the intervention effect both within and between geographic regions. Finally, the use of U5M as the primary outcome, as opposed to intermediate health care delivery indicators and process measures, will allow us to measure the population level impacts of such a CHW-based child health care program at scale.

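### The primary Cox model names no calendar-time adjustment and no time axis; on an age axis it is a within-district before-after contrast that absorbs any common trend

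*Protocol article*

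**What the plan says.** The Statistical analysis section of the protocol article plans a "mixed effects Cox proportional hazards model with a random effect at the community level to estimate effect of the NCHA program on mortality". It then adds district and covariate adjustment: "we will include a fixed effect at the district level. We will also control for baseline demographic and geographic covariates". The district effect has a stated purpose: "To mitigate bias due to unobserved time-invariant confounders that were caused by the non-randomized implementation schedule of the program". The Discussion repeats the community random effect and district effects.

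On follow-up, the same section says: "Children will be included in the risk set from their date of birth or January 2018 (starting date of the panel), whichever is later". Exit is at death, the fifth birthday or the 2022 survey. The section does not say whether the Cox clock is age or calendar date.

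The Abstract describes the aim as to "compare rates of under-5 child mortality between the pre- and post-NCHA program implementation periods". The Implementation section says: "We will take advantage of this staggered implementation to form a study design similar in structure to a stepped wedge cluster randomized trial". The Discussion expects to "compare the intervention effect both within and between geographic regions".

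Two sensitivity analyses are named: a program effect that changes over time, and a restriction to mothers resident throughout. Neither adjusts for calendar time. Secular trend is not among the limitations.

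**The concern.** In every district, time without the program comes before time with it. District effects remove stable differences between districts, and baseline covariates do not change with the calendar. If the Cox clock is age, nothing left in the named model separates the program from the passage of time.

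A stepped-wedge-like design separates the two by comparing reached and unreached districts at the same date. That comparison needs time in the model.

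The document itself gives reasons to expect time effects:

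- a post-Ebola health-system investment plan for 2015-2021, which overlaps the panel;
- COVID-19;
- dependence on recall. The enhanced elicitation covers the last four years, so for interviews later in 2022 the first months of 2018 fall outside it. All time before September 2018 is pre-program.

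At stake is whether the primary hazard ratio measures the program or the calendar.

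**Working it through.** **Inputs from the protocol article.** 20,900 children under five (Study setting and population). Baseline mortality about 100 per 1,000, hazard reduction 25% reached over six months, power 82% (Power calculation). Panel January 2018 to August 2022 (Statistical analysis). Roll-out September 2018 to June 2022 (Implementation), eight districts in four phases (Discussion). Global under-five mortality 93 per 1,000 in 1990 and 38 in 2019 (Introduction).

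**Assumed, because not given.** Two-sided 5% test, two districts per phase, steady births, follow-up of 50 or 56 months, no clustering, and three schedules with first phase September 2018 and last June 2022. The middle two phases are December 2019 and March 2021 (even), March 2019 and March 2020 (early), or September 2020 and September 2021 (late).

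**1. The stated 82%.** It cannot be reproduced exactly, because the test level, variance components and birth rate are not stated and the phase dates are in a figure not available here. Events: 20,900 / 5 × 0.1 = 418 deaths a year at baseline. The fuller calculation gives about 1,620-1,880 over the panel, 28-48% of them post-program. Schoenfeld's formula for the even schedule at 50 months: √(1,670 × 0.35 × 0.65) × |ln 0.75| = 19.49 × 0.2877 = 5.61, and Φ(5.61 − 1.96) is above 99.9%. An expected-count proportional hazards fit on an age axis, with district effects and the six-month ramp, gives 86-98% across schedules without a calendar term. A design effect of about 1.1-2.05 would bring that to 82%.

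**2. Size of the bias on an age axis.** The yearly decline is 1 − (38/93)^(1/29) = 3.0%. In a district that starts at time s in a panel of length T, mean pre-program time is s/2 and mean post-program time is (s + T)/2. They differ by T/2 whatever s is. With deaths spread evenly and a true hazard ratio of 1, ln HR ≈ ln(1 − r) × T/2:

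- T = 50 months: −0.0305 × 2.083 = −0.0635, HR 0.939.
- T = 56 months: −0.0305 × 2.333 = −0.0711, HR 0.931.

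The fits under the three schedules give 0.93-0.94 as well, so the size hardly depends on the unseen dates. At 5% a year the fits give 0.89-0.90. With month effects added, the hazard ratio is 1.00 throughout.

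**3. False-positive rate at 3% a year.** This depends on the standard error (SE).

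| Basis for the SE | SE of ln HR | False positives |
|---|---|---|
| Fits above, no clustering | 0.059-0.073 | 15-24% |
| Separate calculation, five assumed roll-outs, interviews spread over January-August 2022 | 0.054-0.067 | 17-25% |
| Matched to 82% power | 0.08-0.10 | 9-12% at HR 0.94 |
| With calendar terms | 0.084-0.094 | 5% |

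For the third row, SE = 0.2877 / (1.960 + 0.915) = 0.100, or 0.08-0.09 if the ramp dilutes the effect by an assumed 10-20%. At SE 0.100 and HR 0.94, z = 0.0619 / 0.100 = 0.62, and Φ(0.62 − 1.96) + Φ(−0.62 − 1.96) = 9.5%.

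**4. The other axis.** In a small Monte Carlo Cox fit (8 replicates, null program, 8% yearly decline, delayed entry, district effects), the mean hazard ratio was 0.80 on an age axis and 0.99 on a calendar axis.

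**5. Power with calendar terms.** For the even schedule at 50 months, the diluted hazard ratio is 0.786 with SE 0.0661 without calendar terms: 0.241 / 0.0661 − 1.96 = 1.68, power 95%. With month effects it is 0.800 with SE 0.0888: 0.223 / 0.0888 − 1.96 = 0.55, power 71%. Across schedules and calendar terms (linear, quarter or month) the range is 60-73%, before clustering.

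**The case against.** The strongest objection is that the time axis is not stated. On a calendar axis the baseline hazard absorbs any trend shared by the districts, as step 4 shows, and with steady births the missing age term would mainly cost precision. A reader might infer that the model is certainly a before-after comparison that credits all secular decline to the program. The text does not establish that. It makes an age axis the likelier reading, and the pre/post wording of the Abstract fits it.

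The article is also a condensed account and does not claim to list every term, so the list cannot be called complete. What stands is that it states an identification strategy, gives its purpose as time-invariant confounding, and nowhere mentions calendar time, even as a sensitivity analysis or limitation. That goes beyond omitted detail.

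Three other strong readings are not supported:

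- **That staggering contributes nothing.** Even on an age axis it spreads a one-off shock over pre- and post-program time in different districts.
- **That the recall assumption must be false.** The Discussion assumes recall bias "does not differ significantly by geography or intervention status date", which can be read as a statement about differences between areas. Pre-program deaths in late districts can be more recent than post-program deaths in early ones. Forgotten older deaths would bias against the program.
- **That the study has a known false-positive rate.** The 3% is a global average used for illustration. The document gives no trend for rural Grand Bassa, and rising mortality would mask a benefit.

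**Conclusion.** The point holds in conditional form. The primary model names no calendar-time adjustment and leaves the axis open. On the likelier age axis its program hazard ratio absorbs any trend common to the districts, in either direction, and the stepped-wedge-like structure is not used as the Implementation and Discussion sections imply.

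Under the illustrative 3% yearly decline, a null program would show a hazard reduction of 6-7%, about a quarter of the 25% design effect. The chance of false significance would be roughly 9-25%. The hazard ratio rests on the trend, the panel length and an even spread of deaths; the false-positive rate also rests on the assumed roll-out dates and standard error. On a calendar axis the bias from a common trend disappears.

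**What to change.** State the Cox time axis and control both age and calendar time in the primary model, alongside the district fixed effects and community random effect. Either of these would do:

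- an age axis with delayed entry at January 2018, plus calendar-quarter or half-year effects as time-dependent terms;
- a calendar axis with adjustment for age.

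Say that the program effect then comes from comparing reached with not-yet-reached districts at the same calendar time. Report the model without calendar adjustment only as a sensitivity analysis.

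No new data are needed. The cost is precision: in the fits above the standard error rises by about 30-50% with month effects (for example 0.0661 to 0.0888, a ratio of 1.34). Re-run the power simulation under this model and restate the 82%. Because the survey is already a full census of the remote communities, enlarging the sample there cannot recover lost power, so the restated figure should be reported as it stands.
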